8. RESEARCH DESIGN AND METHODS

Data collection in this study will occur on two levels: (1) a mixed, quantitative and qualitative study of the organizations (CBOs) that will implement the *Mujer Segura* intervention, and (2) behavioral and health outcomes for the female sex workers (FSWs) who will participate in the intervention at each CBO.

***The Implementation Process: Organizational Level***

The implementation plan embraces four fundamental principles:

1) Developing local program expertise is important for sustaining model competency and fidelity. Involvement of model developers and practice experts should be front-loaded, then roles shift to local experts as they are developed.

2) Direct coaching and modeling in the actual practice setting is critical for optimal provider skill acquisition.

3) Maintaining and monitoring fidelity across time is critical. Adaptations to the local context or evolutionary changes in the model should be carefully planned, transparent and systematically implemented rather than made idiosyncratically or haphazardly.

4) Policy leadership and funding structures are important for institutionalizing the new practice model.

Phase One: Evaluation of Organizational Characteristics and Training of Staff and Delivery of Comparison Condition Intervention. Two trained ethnographers from the Ciudad Juárez training center will administer computer-based questionnaires to **ten staff (the director, intervention counselors, and supervisors).** The ethnographers will then conduct individual, semi-structured qualitative interviews with each participating staff member, and finally they will carry out a focus group session with all the participants at once in order to assess relevant provider and organizational factors. The questionnaires, the individual interviews, and the focus group session will all last about an hour each, and they will be tape-recorded. Provider factors to be assessed include: attitudes toward adoption of innovation (e.g., intuitive appeal of intervention program); personal disposition (e.g., adaptability, change catalyst); knowledge and perceived utility of intervention; and socio-demographic characteristics. Organizational factors include: leadership qualities; organization culture and climate (e.g., work attitudes, autonomy); organizational support (e.g., support for creativity); and social influence (e.g., teamwork). The same battery of assessments was used by [name] in a study of a children’s service agency (see [name], item 5 in Bibliography). A copy of that assessment battery is provided in Appendix 2. The measures have all been translated into Spanish, and the name of the organization has been changed to fit the new study.

To avoid contamination between the experimental and comparison conditions, CBO staff will first evaluate and deliver the “usual care” counseling session to the control group before learning how to deliver the experimental counseling intervention. A total of 80 FSWs will be recruited at each site, of whom 40 will be randomly assigned to the *Mujer Segura* counseling condition and 40 will be assigned to the usual care risk-reduction counseling condition, which was developed by Mexico’s federal HIV-AIDS agency (CENSIDA) and focuses upon basic educational information, personal risk assessment, and strategies for reducing personal risk. Participants who are randomized at intake to the experimental condition will be asked to return at a later date to receive their assessment and intervention.

Phase Two: Training the CBO’s designated “internal trainer.” Once the comparison condition FSWs have been assessed and counseled, a participating CBO staff member will be designated as the CBO’s “internal trainer” and receive intensive training in both the *Mujer Segura* protocol and in effective methods for teaching the protocol to other staff. Drs. [name], [name], and [name] and two practice experts from the Ciudad Juarez training center will conduct an intensive, eight-day training.

Phase Three: The “internal trainer” trains CBO staff who in turn deliver the *Mujer Segura* intervention. The practice experts will remain at the CBO for two weeks to observe and coach the internal trainer as she trains the counselors who will deliver *Mujer Segura* to the 40 randomized FSWs, and the counselors will begin to deliver the intervention. The experts will give feedback on the delivery and help the CBO counselors resolve challenging or idiosyncratic case issues or presentations. After the practice experts leave, they will maintain weekly telephone and email contact with the CBO counselors.

While the CBO is implementing *Mujer Segura* (over approximately a six-month period), the ethnographers will return periodically to monitor intervention fidelity. Finally, at the end of implementation, the ethnographers will return to repeat the staff qualitative interviews and focus groups that were performed at the outset, in order to enable the researchers to see if any changes have occurred in staff attitudes or organizational characteristics over the course of implementing the intervention.

Phase Four: Maintenance. In the fourth and final phase of the implementation model, the internal trainer will shift roles to maintenance. Maintenance activities include training and coaching new hires, a lower level of in vivo coaching and fidelity monitoring of existing trainees (quarterly rather than weekly or bi-weekly), and planning any major adaptations or evolutionary modifications of the model.

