We evaluated statistical power to detect main effects and interaction effects in Hypotheses 3 and 4. Our power analyses reveal that we have an excellent chance of detecting significant main effects and interactions in our data. Hypothesis 3 uses a repeated measures design with two conditions. Assuming an attrition rate of 20%, which we achieved in *Mujer Segura*, we will have 384 subjects per group for a total of 768 subjects at the end of five years. We used findings from the parent project intervention with FSWs described in Preliminary Studies to estimate overall reductions in high-risk sex and incident STIs. We observed a 36% reduction in unprotected sex in the intervention (i.e., 18% vs. 36%), and a 40% decrease in overall STI incidence in the intervention group relative to the control (i.e., 20% vs. 38%). To estimate power in our sample, assuming a 36% reduction in unprotected sex at six-month follow-up, we calculated the following: N=384 per group, alpha = .05, and a 36% reduction in mean number of unprotected sex acts. If subjects in our experimental condition reduced the number of unprotected sex acts while the control condition did not change (i.e., group x time interaction), we would detect significant differences greater than 78% of the time. Power is slightly higher for STIs (i.e., .81). The addition of a covariate for fidelity to test hypothesis 4 does not substantially impact power estimates. Therefore, though our study is not designed to replicate findings from the parent project, we have sufficient power to detect differences between groups.

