***Intervention Study Participants (FSWs)***

The second set of participants in this research will be the FSWs who are recruited at each CBO to participate in the baseline and follow-up assessments and either the *Mujer Segura* counseling intervention or the “usual care” comparison condition. The recruitment goal for the study will be 960 female sex workers (FSWs) from the twelve anticipated sites (12 CBOs times 80 FSWs per site = 960). As with the staff participants (see above), we are uncertain whether the all of the currently projected sites will be able to meet this quota. We also face the uncertainty (particularly in the early phases of the study) whether, once the study has been started at a particular site, the staff will be able to carry it to completion due to factors beyond our or Mexfam’s control. Accordingly, we request flexibility in the per-clinic and overall figures for recruiting FSWs, up to a maximum of 1,090 for the entire study (in increase of 130, which is 13.5% more, or the equivalent of less than two additional sites).

We anticipate that participants will range in age from 18 to 50 years (mean approx. 33); mean level of educational attainment will be 6 years; 80% will be married or living in a common-law relationship; and 94% will have children.

Inclusion Criteria: To be eligible for this intervention, participants must be:

1) Biologically female,

2) At least 18 years old,

3) Report having exchanged sex for money, goods or drugs within the previous 30 days,

4) Report having unprotected vaginal or anal sex with a male client at least once during the previous month.

Exclusion Criteria:

1) Consistent use of condoms for vaginal and anal sex with all male clients during the previous month,

2) Known to be HIV+ or test HIV+ for the first time on-site at MexFam clinic,

3) Being under 18 years of age,

4) Being male or transgendered,

5) Being incapable of giving informed consent,

Because this study is designed to transport an established, efficacious intervention into a community-based setting, we must adhere to core elements of the established intervention, which was designed for women who are biologically female. In the original intervention design, transgendered persons were excluded because this subpopulation of FSWs would require different recruitment strategies and a targeted intervention to reflect unique sexual risk behaviors and sexual milieu.

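### The experimental arm's baseline is deferred to a return visit after randomisation, so baselines differ in timing and only that arm can lose women before baseline

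*Protocol*

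**What the plan says.** Protocol Section 8, The Implementation Process: Organizational Level, sets the order of events at each site.

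- To avoid contamination, "CBO staff will first evaluate and deliver the “usual care” counseling session to the control group before learning how to deliver the experimental counseling intervention". Of 80 women per site, 40 are randomised to each condition.
- For the experimental arm: "Participants who are randomized at intake to the experimental condition will be asked to return at a later date to receive their assessment and intervention".
- The second phase begins "Once the comparison condition FSWs have been assessed and counseled". The trainers then "conduct an intensive, eight-day training" for the internal trainer, who next trains the counsellors. The delivery period is described as follows: "While the CBO is implementing *Mujer Segura* (over approximately a six-month period").

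Section 8, The Intervention: Level of the FSW, places the baseline data before counselling and the second assessment at six months. HIV and STI tests are done at those same two points.

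The Aims 3 & 4 analysis enters condition, time and their interaction as the primary terms. For power it takes 20% attrition, as in the parent study, and concludes "we will have 384 subjects per group for a total of 768 subjects at the end of five years".

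Eligibility (Section 9) has time-bound and test-bound criteria, among them "Report having unprotected vaginal or anal sex with a male client at least once during the previous month" and, as an exclusion, "Known to be HIV+ or test HIV+ for the first time on-site at MexFam clinic".

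Section 17 describes one initial visit holding interview, counselling and STI testing. Section 18 pays for two visits, baseline and six months.

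**The concern.** The text defers the assessment as well as the counselling, and only in the experimental arm. Nothing gives those women an interview or test at intake. Two consequences follow from the plan as written.

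1. **Unlike baselines.** Control baselines are taken in the first phase at a site. Experimental baselines are taken after randomisation, after a wait of unstated length and in a later calendar period. The group-by-time term uses each arm's own baseline as its starting point, so anything that changes during the wait enters the treatment estimate.
2. **One-sided loss before baseline.** An experimental woman who does not come back contributes no baseline, and the plan does not say whether she is sought at six months. A control has no such gap to fall into. The analysed experimental set is therefore selected after randomisation.

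At stake is Aim 3, the protocol's only randomised comparison. An analysis plan can define populations and handle missing outcomes, but it cannot supply intake data that were never collected.

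**Working it through.** **Sequence.** For any experimental woman the wait covers the rest of the control phase, the eight-day training and the counsellors' training. It may extend into the delivery period of about six months. The protocol gives no total.

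**The plan's own number.** 12 sites × 40 = 480 per arm, and 480 × (1 − 0.20) = 384. This reproduces, provided both arms lose 20% of those randomised.

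**Waiting loss (assumption).** Let a share L of experimental women never return, with 20% attrition afterwards: n_E = 480 × (1 − L) × 0.80.

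The protocol gives no SD and, in this paragraph, no sidedness. I therefore back-solve the standardised effect that gives .78 power at 384 per arm, two-sided .05, women treated as independent: d = (1.960 + 0.772) × √(2/384) = 0.197. Then power = Φ(d/√(1/n_E + 1/384) − 1.960).

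| L | n_E | Randomised women retained (controls 80%) | Power |
|---|---|---|---|
| 0 | 384 | 80% | .78 |
| 10% | 345.6 | 72% | .76 |
| 20% | 307.2 | 64% | .73 |
| 30% | 268.8 | 56% | .70 |

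**What selective non-return could do to the STI comparison (assumption).** Suppose no treatment effect, the 38% control risk from the power paragraph in both arms as randomised, and non-returners at k times the returners' risk. The returners' risk is r = 0.38/(1 − L + L × k). For L = 20%:

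- k = 1.25: 0.38/1.05 = 36.2%
- k = 1.5: 0.38/1.10 = 34.5%
- k = 2: 0.38/1.20 = 31.7%

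With n_E against 384 controls, a nominal 5% two-sample test of proportions (pooled standard error under the null) rejects as follows:

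| L | k = 1.25 | k = 1.5 | k = 2 |
|---|---|---|---|
| 10% | 6% | 8% | 16% |
| 20% | 8% | 15% | 41% |
| 30% | 11% | 25% | 64% |

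If non-returners had lower risk, the bias would run the other way.

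**Regression to the mean.** Women are selected on unprotected sex in the month before screening. If the interview uses a similar recall, the control baseline lies nearer that selected month than the experimental baseline does. The protocol gives no recall period, no dispersion of counts and no re-screening rule, so no single size can be stated. In null simulations with gamma-Poisson monthly counts (mean 3 to 20 acts), the spurious difference ran from under 1% to about 35% of the control baseline, depending on the parameters. Re-applying the one-act criterion on return brought rejection to about 3–7%. This is illustration only, and the conclusion does not rest on it.

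**HIV exclusion timing.** At the 2 per 100 person-years given in Section 6 and an assumed three-month wait, 480 × 0.02 × 0.25 = 2.4 women. This is minor.

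**The case against.** The staggered order has a stated and sensible reason, contamination. The FSW outcomes are called a secondary aim in Section 8, and the staff are named as the primary participants. Non-returners and analysis sets are commonly settled in an analysis plan, which is not shown. A six-month between-arm comparison needs no baseline at all. Recruitment may rise to 1,090, and those 130 extra women exceed the 480 × 0.20 = 96 who would be lost at 20% non-return.

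Part of this stands. Power is not the main problem: even 20% waiting loss moves it only from .78 to .73, and extra recruitment would help the numbers. It would not remove selection, though. The contamination argument covers the counselling and the staff training but gives no reason to delay the interview. A comparison at six months alone is not the planned test, and it still needs outcomes on women who never returned.

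A reader might infer more than the documents support:

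- *That randomisation has failed.* Allocation remains random. What is lost is its protection of the baseline and of the analysed set.
- *That the bias has a known direction*, such as a spurious fall in controls or falsely low STI incidence in the experimental arm. Either is possible, but neither is shown.
- *That the 20% attrition covers only follow-up after the wait.* The power paragraph applies 20% to all 480 and does not say when losses occur. The plan makes no separate allowance for the wait, and no more can be said.
- *That the HIV exclusion materially unbalances the arms.* Field screening is common to both, and the numbers involved are very small.

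**Conclusion.** The point holds as a design defect. As written, the experimental arm has a later, post-randomisation baseline, and it alone can lose women before baseline. The group-by-time test inherits both features. The magnitude and net direction of the bias cannot be determined from the protocol, so neither a positive nor a null Aim 3 result could be read cleanly. The figures 346/307/269 and .76/.73/.70 rest on assumed waiting losses of 10/20/30% added to 20% attrition. The STI figures rest further on an assumed risk ratio in non-returners. Sections 17 and 18 do not sit easily with an intake followed by a return visit. If their initial visit is read as the return visit, they fit better, but that reading confirms that the experimental arm has no intake data. The change belongs before enrolment, because the missing data cannot be recovered afterwards.

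**What to change.** 1. Give the baseline interview (about 30 minutes) to all 80 women per site at intake, before allocation is disclosed, and settle behavioural eligibility there.
2. Use the intake values as the baseline covariate for both arms in a between-arm comparison at six months that keeps every randomised woman, including non-returners. If the short behaviour items are repeated before the delayed session, use them descriptively only, since only one arm has them.
3. Take baseline HIV/STI specimens at intake in both arms where feasible. Otherwise, state that the STI comparison remains exposed to waiting loss.
4. State the follow-up clock for each arm, including for women who never return.
5. Restate the expected experimental number and power under an explicit waiting-loss assumption.
6. Reconcile Phase One, the baseline definition in The Intervention: Level of the FSW, and Sections 17 and 18.

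**Cost.** The intake visit is longer for about 480 women, and the baseline payment may have to be split. The interval from baseline to follow-up is longer in the experimental arm by the length of the wait. If specimens move to intake, that arm also has more time at risk before counselling, so the incidence analysis must state which interval it counts. Delayed counselling and the protection against contamination are unchanged.

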5. SPECIFIC AIMS

This project builds upon [name] earlier study, “Safer Sex Intervention for Female Sex Workers in Mexico” (Project #051182). In that study, we developed a brief behavioral intervention to promote condom use and enhance safer-sex negotiation skills among FSWs in Mexican border cities. The intervention (named *Mujer Segura* in Spanish) was recently demonstrated to be efficacious, mediated by improvements in FSW self-efficacy (see “Progress Report”).

As a result, the federal government in Mexico expressed interest in scaling up the intervention across Mexico and encouraged us to conduct a formal evaluation of the implementation process in order to learn how most effectively to implement this type of intervention throughout Mexico. Therefore, we propose to test a train-the-trainer model for transporting *Mujer Segura* into existing Community Based Organizations (CBOs) in Mexico. This model seeks to develop local and culturally relevant expertise and infrastructure to further disseminate and maintain *Mujer Segura* within each CBO. We will examine whether this model can develop a network of HIV/STI prevention services for FSWs with self-sustaining levels of model fidelity and provider competency. Levels of fidelity to the intervention protocol as well as the efficacy of the intervention itself will be measured at each stage to see how well fidelity and efficacy are preserved through the process.

Our specific aims and corresponding hypotheses are as follows:

Aim 1: To determine if the train-the-trainer implementation model can achieve and sustain high levels of intervention model competency and fidelity.

Hypothesis 1. Competency and fidelity as measured by direct observation methods and FSWs’ reports will achieve at least 90%.

Aim 2: To characterize the relationship between individual provider characteristics and organizational factors, and their impact on the implementation of our intervention, using a mixed-methods (quantitative/qualitative) approach.

Hypotheses 2a –2f: Specific quantitative hypotheses to be examined include:

2a) More positive organizational culture and climate will be associated with more positive attitudes toward evidence-based interventions (EBI).

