***The Intervention: Level of the FSW***

A secondary aim of this study is to determine how FSW behavioral outcomes change concordant with the fidelity of the implementation of *Mujer Segura* at each CBO and with other organizational characteristics. FSW data will be gathered at baseline (prior to counseling) and again at six-month follow-up using measures employed in our previous work with Mexican FSWs (Project #051182), which was reviewed and approved by the IRB.

Baseline and Follow-up Interview. The baseline interview (~30 min) is theory-driven and has been administered to over 1,800 FSWs in Mexico-U.S. border cities. Per the recommendations of our Mexican collaborators, all measures will be administered by computer-assisted personal interviewing (CAPI). Reading ability is not a requirement of study participation. Using CAPI technology, the interviewer will read all questions and response categories to the participant and record the participant’s responses on a computerized form.In order to measure intervention effects, the interview will be repeated with each participant at a six-month follow-up appointment. The interview covers the following domains:

 Background Characteristics. These include socio-demographics, family background variables (e.g., number of children), and financial need (e.g., number of financial dependents).

 Contextual factors. Interview questions include working conditions: work setting (e.g., street), type of sex worker (e.g., brothel-based), nature of relationship with pimp or manager (if applicable) (e.g., control over client selection), client characteristics, demands for unprotected sex, amount received for protected vs. unprotected sex, and availability of condoms and sterile syringes.

 Substance Use. History, practices and environmental influences, including age at first use of alcohol and specific drugs, amount of alcohol consumed using the AUDIT; types of substances used alone and in combination, routes of administration, and injection practices.

 Mechanisms of Change. Consistent with our theoretical framework, we include measures of attitudes, intentions, and peer norms about safer injection and sex.

 HIV and STI Knowledge will be measured with an 18-item scale that assesses awareness of the importance of condom use with respect to HIV/STI prevention (alpha = 0.75 to 0.89).

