4) To guard confidentiality, all questionnaire data will be in stored in computerized form with ID numbers only (no names). Computers will be stored in locked offices at MexFam CBOs and UCSD. **Contact information for enrolled participants (locator form) will be stored in a locked file cabinet in the director’s office at each CBO; the locator form will not have the participant’s identifier number. Locator forms will be shredded at the completion of six-month follow-up, unless the participant has indicated on her consent form that she is willing to be contacted for additional studies; in this case, the locator form will be retained under secure conditions for an additional two years and shredded at the end of that period. Original signed consent forms will be stored in a locked file cabinet in the Project Official’s office at MexFam in Mexico City. A copy of all consent forms will be shipped to San Diego for permanent storage in a locked file cabinet in [name] office. Digital audio-recordings of intervention sessions with FSWs made for training and quality-assurance purposes will be stored on password-protected computers and will not be labeled with any information that identifies the FSW. The key to participants’ code numbers (name-to-ID relational file) will be encrypted in a computer file, which will be locked in the director’s office at each MexFam CBO and in [name] office in San Diego. Only the CBO directors, Drs. [name] and [name], and the USCD data manager will be able to un-encrypt the computer file. Other security mechanisms at the MexFam CBOs and UCSD include: security workshops and written security policies and procedures.**

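### Hypothesis 1 relies on FSW reports of fidelity that no visit collects, and the only research staff assigned to fidelity are the unblinded ethnographers who gather the staff attitude data used in 2d and 2e

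*Protocol*

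**What the plan says.** **Fidelity sources.** Section 5 (Specific Aims), Hypothesis 1: "Competency and fidelity as measured by direct observation methods and FSWs’ reports will achieve at least 90" percent.

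**FSW data.** Section 8, The Intervention: Level of the FSW: "FSW data will be gathered at baseline (prior to counseling) and again at six-month follow-up". The six-month interview repeats the baseline one. Its listed domains are background, working context, substance use, mechanisms of change (knowledge, self-efficacy, norms, attitudes to prevention, expectancies) and sexual risk behavior. Section 17 (Expense to Subject) gives the content of the two visits as interview, counseling and STI testing at the first, and repeat interview and STI testing at the second.

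**Staff attitudes.** Section 8, Phase One: two ethnographers "will administer computer-based questionnaires to" ten staff per CBO. "The ethnographers will then conduct individual, semi-structured qualitative interviews with each participating staff member", followed by a focus group. On content: "Provider factors to be assessed include: attitudes toward adoption of innovation", together with disposition and perceived utility. Section 14 (Risk Management Procedures, CBO Staff) leaves the gathering and handling of the organizational data to ethnographers from the Ciudad Juárez site alone.

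**Fidelity during implementation.** Section 8, Phase Three: "the ethnographers will return periodically to monitor intervention fidelity". At the end, "the ethnographers will return to repeat the staff qualitative interviews and focus groups that were performed at the outset".

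**Recordings.** Section 14, FSW Intervention Participants, mentions "Digital audio-recordings of intervention sessions with FSWs made for training and quality-assurance purposes". They are not assigned to fidelity scoring.

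**The concern.** There are two linked problems.

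First, Hypothesis 1 commits the study to two fidelity sources, but the data collection provides for only one. FSW reports are also the source that does not depend on the study's own observers, so their absence leaves observation without a cross-check.

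Second, the people sent to look at fidelity already know, from an hour-long interview and a focus group, how each participating counselor feels about the intervention. Hypothesis 2e tests whether more positive attitudes go with higher fidelity. Hypothesis 2d uses the same link as the second path of a mediation. If an observer's impression of an enthusiastic or sceptical counselor colours the fidelity assessment, part of the tested association could arise from the measurement.

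**Working it through.** **Step 1. Is an FSW fidelity report collected anywhere?**
- Baseline interview: held before counseling, so it cannot report on the session.
- Six-month interview: a repeat of the baseline interview, with no listed domain on the session or the counselor.
- Section 17: no other assessment at either visit.
- Result: the source named in Hypothesis 1 has no collection point.

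**Step 2. Who assesses fidelity, and what do they know?**
- Attitude questionnaires, individual interviews and focus group: the ethnographers (Phase One).
- Handling of those data: ethnographers from the same site, exclusively (Section 14).
- Fidelity during implementation: the ethnographers (Phase Three).
- Number of ethnographers: two (Phase One; also Qualitative Analyses).
- Blinding, separation of roles or a second independent rating: none described.
- The Aim 1 analysis text mentions fidelity ratings without naming a rater.

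**Step 3. Reproduce the plan's power for the 2e correlation.** Inputs from Data Analysis and Interpretation, Aims 1 and 2: total N 96, cluster size 8, ICC .03, r = .30, two-sided alpha .05.
- Design effect = 1 + (8 − 1) × .03 = 1.21; functional N = 96 / 1.21 = 79.34.
- Power = Φ(d − 1.96) + Φ(−d − 1.96), with d = [atanh(r) + r / (2(N − 1))] × √(N − 3).
- N = 96: .851 (plan: .85). N = 79.34: .777 (plan: .78).

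The stated power reproduces, so there is no power error here.

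**Step 4. Illustration of what a small induced correlation would do.** Assumption, not in the protocol: the true attitude–fidelity correlation is zero, and observer expectation alone induces a correlation r. Using d = atanh(r) × √(79.34 − 3) = atanh(r) × 8.737:

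| Induced r | d | Rejection at nominal 5%, N = 79.34 |
|---|---|---|
| .05 | 0.44 | about 7% |
| .10 | 0.88 | about 14% |
| .20 | 1.77 | about 43% |

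The table shows sensitivity only. It does not estimate the bias in this study.

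**The case against.** The case against is substantial, and several parts of it stand.

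- *The protocol says monitor, not rate.* Correct. No passage says who produces the analysed fidelity score or with what instrument, so a reader who takes it as stated that the ethnographers rate fidelity goes beyond the text. It remains an inference. It is a reasonable one, because Hypothesis 1 requires direct observation and no other research staff are assigned to measure fidelity during implementation.
- *Others also observe.* Practice experts observe and coach on site for two weeks, the internal trainer monitors fidelity in the maintenance phase, and sessions are recorded. None of these is presented as a study measurement, but they mean that the ethnographers are not the only people who see delivery.
- *Predictor and outcome do not come from one rater.* Correct. A reader might infer shared-rater variance, but attitudes are the staff member's own answers on a computer-based questionnaire. Bias could enter only through the fidelity side.
- *Knowledge at the time of observation may be faint.* Attitudes are measured in Phase One, before usual care is delivered and before *Mujer Segura* training, and two people see about 12 × 10 = 120 staff. The transcript coding is not dated relative to the fidelity visits, so it does not show that coded results were known by then. The interviews and focus group alone still give the observers that knowledge.
- *A fidelity form for FSWs may simply be undescribed.* Possible, since the protocol describes no fidelity instrument. But it does list the visits and their content, and a report on the session fits into neither.

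An unseen SAP would not settle these points. What women are asked, when, and who observes whom are matters of data collection, and analysis cannot supply a report that was never taken.

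**Conclusion.** The point holds in two parts of different strength. The firmer part is an internal inconsistency: Hypothesis 1 names FSW reports as a fidelity source, and the scheduled visits collect none. It needs no assumption beyond reading the visit content as complete.

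The second part is a risk, not a demonstrated bias. Hypotheses 2d and 2e are exposed to observer expectation because the only research staff assigned to fidelity during implementation also collect and handle the attitude data, with no blinding. This rests on the inference that their observations form the analysed score. The size of any bias cannot be derived from the protocol, and the 7% to 43% range is illustrative.

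The scope is limited. The randomized comparison in Aim 3 is unaffected. Hypotheses 2f and 4 use fidelity but do not depend on the attitude link. A reader might also infer that mean fidelity against the 90% target is biased, but nothing in the protocol shows this. The change is worth making because it is cheap and cannot be made after the data are collected.

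**What to change.** 1. **Name the source of the fidelity score and separate the roles.** State in Section 8 who produces it. At each CBO, have it rated by the ethnographer who did not administer the questionnaires to, or interview, that CBO's staff, took no part in its focus group, and does not see or code its attitude data until the ratings are final. Alternatively, have the existing session recordings scored under the same restriction, with their stated purpose in Section 14, and consent, extended to cover it.
2. **Supply or remove the FSW report.** Add a brief yes/no checklist of session components, read to each *Mujer Segura* woman right after counseling by someone other than her counselor. Otherwise, delete FSW reports from Hypothesis 1.

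**Cost.** Staff interviewing at each CBO becomes slower because one ethnographer does it, and the order of transcript coding is constrained. The checklist needs a short new Spanish form and a few minutes for each of about 12 × 40 = 480 women. It must be read aloud, since literacy is not required for participation. The rest is protocol wording.
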